#### **Statistical Methods**

Study conditions will be compared on baseline demographics and other characteristics using analysis of variance (ANOVA) for continuous variables and chi-square tests for categorical variables. If a specific characteristic differs significantly across study conditions and is predictive of the outcome, it will be considered as a potential covariate in subsequent analyses. Analyses of treatment effects on smoking status will adhere to an intent-to-treat approach whereby all women randomized to each study condition will be included in the analyses independent of early dropout, noncompliance, etc., with the exception of women excluded for abortion/fetal demise as is convention in this research area. Cochran-Mantel-Haenszel tests (C-M-H) will be performed for comparisons between the incentives vs. usual care conditions on point-prevalence smoking abstinence at end-of-pregnancy and 6-months postpartum assessments with referring clinic as a stratification variable. The Breslow-Day Test will be used to examine the homogeneity of treatment effects across referring clinics. Comparisons of point-prevalence abstinence rates between treatment conditions across all assessments through six months postpartum will be analyzed using mixed model repeated measures for categorical data based on generalized estimating equations (GEE) using a logistic link function (SAS: PROC GENMOD, SAS Institute, Cary, NC). The two treatment groups will also be compared on birth outcomes, breastfeeding, and other measures collected postpartum. Comparisons of treatment conditions on dichotomous outcomes (e.g., % low birth weight, % preterm, % NICU admissions, % breastfeeding) will parallel categorical analyses for point prevalence abstinence using PROC GENMOD to adjust for strata (referring clinics) and potential covariate effects. Analysis of covariance (ANCOVA) will be used to compare study conditions on mean birth weight adjusting for variables known to influence birth weight (% maternal pre-pregnancy BMI, parity, and sex) and mean gestational age at delivery. The significance criterion will be set at  $\alpha = 0.05$  for all analyses.

Regarding the cost-effectiveness analysis (CEA), the CEA will be conducted by dividing the average (mean) difference in treatment costs across the incentives versus best practices conditions by the average (mean) difference in each outcome (abstinence rates in late pregnancy, birth outcomes) to derive incremental cost-effectiveness ratios (ICERs). Statistical significance of these ICERs will be determined probabilistically by employing non-parametric bootstrapped standard errors. The main objectives of this preliminary CEA will be to (a) establish methods for obtaining and analyzing data that pertain to both treatment delivery and birth outcomes in remote financial incentives interventions, and (b) comparing ratios on key birth outcome measures and NICU admissions. These basic CEA data will provide important preliminary data for a future RO1 application in which we may propose conducting a more sophisticated cost-effectiveness analysis that incorporates both birth outcomes and infant health outcomes assessed over a longer time period (e.g., medical illnesses throughout the infant's first year of life).

Regarding the acceptability data, TAQ items administered using a 100-point VAS will be compared across the two treatment conditions using ANOVA's. Again characteristics that differ across treatment condition will be considered as potential covariates. Responses to the semi-structured interview questions will be transcribed directly during the interview and analyzed afterwards using a thematic content analysis. We will employ an inductive approach whereby the content of these qualitative data will direct the coding and theme development. Coding of the data will involve grouping, sorting, and identifying themes that reflect barriers and facilitators of treatment engagement. Two researchers will perform the content analysis independently and sort responses into

themes. Disagreements will be resolved through discussion until consensus is reached. Those themes that emerge and reflect modifiable aspects of the intervention (e.g., provision of technical support, appropriateness of staff counseling and feedback surrounding quitting smoking) will be taken into account in designing future iterations of this intervention that are more responsive to participant's preferences.

Comparable analyses may be conducted among the smaller subset of AI/AN pregnant women. However, as financial-incentives-based interventions to promote smoking cessation have never previously been examined among this subgroup using either in-person or remote methods of treatment delivery, this additional subset of pregnant women is more exploratory at this stage, and provides an important opportunity to conduct a feasibility and proof of concept assessment. As our examination of the intervention among a subgroup of AI/AN women represents the first feasibility and proof of concept assessment to our knowledge, power analyses were not conducted to determine the sample size needed to obtain statistically significant effects on the above outcomes. However, once we complete our assessment of the feasibility and efficacy of smartphone-based financial incentives among this subset of AI/AN women, such analyses will be conducted to determine the sample size needed in future, larger-scale studies targeting this unique subpopulation.

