**Assessment Battery** Participant's intake assessment will be conducted after they have had their first prenatal visit and phone screen to determine preliminary eligibility and will address six areas: (a) Sociodemographics (age, educational attainment, race/ethnicity, marital status, health insurance status); (b) Medical/pregnancy history (height/weight, self-reported pre-pregnancy weight, weeks pregnant, history of complications in prior pregnancies; (c) Smoking history (age started smoking, pre-pregnancy time to first cigarette/cigarettes per day, past week time to first cigarette/cigarettes per day, number of quit attempts before/during the current pregnancy, number of other smokers in the household, rules about smoking in the household, nicotine dependence); (d) Smoking timeline follow-back (to characterize daily smoking rates and/or use of alternative tobacco products or nicotine replacement therapy since learning of the current pregnancy); (e) Smoking attitudes (motivation to stop, confidence in ability to stop, intention to quit before the baby is born, intention to remain abstinent after the baby is born, perceived stress levels); (e) Maternal health/executive functioning (lifetime history of depression, general psychiatric symptoms, current depressive symptoms, discounting of delayed hypothetical monetary rewards, behavioral economic measure of the reinforcing value of cigarettes, Behavior Rating Inventory of Executive Function®-Adult Form [BRIEF-A; see attached], EQ-5D Health-Related Quality of Life Questionnaire [see attached]); (f) Stressful life events (SAMHSA Life Events Checklist [see attached]). Appropriately modified versions of these measures will be administered at the other six formal assessments identified above. In addition, at the postpartum assessments we will assess breastfeeding, including initiation, duration, and different levels of breastfeeding (e.g., exclusive, predominant, any).

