#### Sample Size Justification

Based on data from (a) our prior and ongoing trials which utilized a comparable schedule of routine smoking monitoring visits and schedule of potential earnings, and (b) previous trial data indicating a 20% decrease in abstinence rates from late pregnancy to 24-weeks postpartum, we expect late-pregnancy abstinence rates of approximately 40% vs. < 10% (incentives vs. best practices, respectively), and 24-week postpartum abstinence rates of approximately 20% vs. < 5%. The proposed sample size of 76 per treatment condition will result in at least 80% power to detect a difference between the two treatment conditions in abstinence rates of 40% vs. 10 % at late-pregnancy or 20% vs. 5% at 24-weeks postpartum assessments using a chi-square test. This proposed sample size is also expected to be more than sufficient for examining differences between treatment conditions in birth weight and breastfeeding outcomes. With respect to mean birth weight, power is estimated to be 60% to detect a difference of approximately 200 g between the incentives versus best practices conditions assuming a pooled standard deviation (SD) of 550 g, which aligns well with treatment effects in our study aggregating birth outcomes across our first three controlled trials whereby mean birth weights were  $3295.6 \pm 588$  g vs.  $3093.6 \pm 404$  g in the incentives versus control conditions, respectively. We are estimating breastfeeding rates of 50% and 30% in the incentives condition and 17% and 13% in the best practices condition at 12 and 24-weeks postpartum based on our prior study results. Using chi-square tests, we will have over 75% power to detect differences in breastfeeding rates between the incentives versus best practices conditions at the two assessments. Power calculations were done using a two-sided significance level of 0.05. A sample size of 60 for the arm targeting AI/AN women was selected based on initial pilot studies of the financial-incentives-based approach to promoting smoking cessation among pregnant women developed at the University of Vermont (Higgins et al., 2004). This sample size will be sufficient to determine whether the intervention is feasible and effective at promoting late-pregnancy smoking abstinence between AI/AN women enrolled in the Incentives versus Best Practices Control conditions. Results of our assessment will be used to inform power analysis calculations for larger-scale, NIH-supported research proposals focused on smoking cessation among AI/AN pregnant women.

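### Choosing covariates by testing randomised arms for baseline differences adds no precision and leaves the GEE/GENMOD and acceptability models to be settled after the data are seen

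*Protocol*

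**What the plan says.** The Protocol's Statistical Methods section opens with between-arm tests at baseline: "Study conditions will be compared on baseline demographics and other characteristics using analysis of variance (ANOVA) for continuous variables", with chi-square tests for categorical variables. The list of characteristics is open-ended. It continues: "If a specific characteristic differs significantly across study conditions and is predictive of the outcome, it will be considered as a potential covariate" in later analyses. A characteristic must therefore be both imbalanced and predictive, and even then is only considered. An alpha of 0.05 is set for all analyses, which I read as covering the baseline tests.

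For the acceptability questionnaire, later in the same section, only the first condition remains: "Again characteristics that differ across treatment condition will be considered as potential covariates".

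The abstinence outcomes have two kinds of analysis. The Cochran-Mantel-Haenszel (C-M-H) tests at end of pregnancy and six months postpartum name referring clinic as the only stratifier. The repeated-measures comparison uses GEE in PROC GENMOD, and the dichotomous birth and breastfeeding outcomes follow it with allowance for potential covariates. Only the birth-weight ANCOVA names prognostic covariates in advance (BMI, parity, sex, and apparently gestational age).

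The Assessment Battery shows that intake already records smoking history, including "past week time to first cigarette/cigarettes per day", the pre-pregnancy equivalents, quit attempts and nicotine dependence.

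**The concern.** When allocation is random, a baseline difference between arms is chance by construction, and its p-value does not say whether adjustment is useful. What matters is how strongly the variable predicts the outcome. By requiring imbalance first, the rule discards nearly every prognostic variable before its prognostic value counts.

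Both conditions are also judged on trial data, over an unspecified list, with a final discretionary step. The covariates in the GEE/GENMOD and acceptability models are thus settled after the data are seen. In a logistic model this also changes the quantity reported, because covariate-adjusted and unadjusted odds ratios are not the same parameter.

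At stake are a modest amount of precision where power is tightest, at 24 weeks postpartum, and the credibility of models that should have been fixed beforehand.

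**Working it through.** **Inputs from the Protocol.** 76 per arm; abstinence 40% vs 10% in late pregnancy and 20% vs 5% at 24 weeks postpartum; chi-square test; two-sided 0.05 (Sample Size Justification). Equal allocation (Consent Procedures).

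**Assumed, because the Protocol gives no figures.** The number of baseline variables tested, and predictor strength as log-odds per SD.

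**1. Stated power.** With pooled p̄, power = Φ[(Δ − 1.96·√(2p̄(1−p̄)/n)) / √((p₁(1−p₁)+p₂(1−p₂))/n)].
- 20% vs 5%: p̄ = 0.125; (0.15 − 1.96 × 0.05365)/0.05225 = 0.858; power 80.5%.
- 40% vs 10%: p̄ = 0.25; (0.30 − 1.96 × 0.07024)/0.06589 = 2.46; power 99.3%.

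Both agree with the stated minimum of 80%. The 24-week comparison has no slack.

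**2. How often the rule can act.** Each baseline test is significant 5% of the time. With k independent tests, the chance of at least one is 1 − 0.95^k: 40% for 10, 54% for 15, 64% for 20, 79% for 30. Some imbalance is therefore likely. With two prognostic variables, however, the chance that either is imbalanced is only 1 − 0.95² = 9.75%, however strong they are. The prediction condition can only lower that.

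**3. Simulated power, 20% vs 5%, 76 per arm.** Simulation A: 4,000 trials per setting, logistic Wald test, 15 independent covariates of which two are prognostic, simulation error about 0.6 points. Simulation B: a separate run with two predictors. Compare within rows; the set-ups differ.

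| Simulation, log-odds per SD | No adjustment | Protocol rule | Two covariates fixed |
|---|---|---|---|
| A, 0.5 | 78.6% | 78.5% | 81.2% |
| A, 0.8 | 79.4% | 79.2% | 84.1% |
| B, 0.3 | 84% | 84% | 86% |
| B, 0.5 | 83% | 83% | 85% |
| B, 0.8 | 83% | 83% | 87% |

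A prognostic covariate passed both conditions in about 3–9% of trials across all settings of A, and the rule triggered in 2–8% in B. In A at 20% vs 5%, the rule selected some covariate in 9.5% and 12.2% of trials but a prognostic one in only 4.4% and 7.7%. In the remainder (about 5% and 4.5%) it picked only noise.

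**4. Late pregnancy, 40% vs 10%.** In A all three approaches exceed 99%.

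**5. Type I error.** In A under the null, the rule rejected in 1.0–4.9% of trials, with no adjustment in 1.1–5.1%, and with two fixed covariates in 1.4–5.0%.

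**6. Room for covariates.** Expected abstinent women at 24 weeks: 76 × 0.20 + 76 × 0.05 = 15.2 + 3.8 = 19. Treatment plus two covariates leaves 19/3 = 6.3 events per term; treatment plus four leaves 19/5 = 3.8. In further likelihood-ratio runs with four covariates, null rejection was 5.5–6.1% at a common 12.5% rate and 7.2–7.8% at a common 5% rate, while the unadjusted chi-square stayed at 4.7–5.6%.

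**7. Weak predictors.** In those same runs the gain was under 1 point: one predictor at 0.3, 84.6% to 85.2%; four covariates at 0.3/0.3/0/0, 83.5% to 84.3%; four at 0.2/0.2/0.2/0, 82.6% to 83.3%.

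**The case against.** The strongest reply is that little is harmed. The stated power belongs to an unadjusted chi-square test, the C-M-H tests name no covariate beyond clinic, and the rule leaves power where it was. A reader might infer that the trial loses part of its planned 80%, or that the C-M-H results turn on which baseline tests cross 0.05. The documents support neither. An optional gain is not taken, and the rule acts mainly on the GEE/GENMOD and acceptability analyses.

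A reader might also infer that picking chance imbalances inflates false positives. It does not in the settings examined, and the prediction condition, where it applies, screens out most irrelevant variables.

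Nor does the Protocol show that the intake smoking variables are strong predictors. It lists them without effect sizes, and with weak predictors the gain is within simulation error. Too many covariates would also bring a size problem of their own. Both points stand and limit the remedy.

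Finally, a covariate list is commonly left to the SAP, so its absence is not the fault here. That does not excuse the rule: the Protocol states it, in two places, and a SAP would have to inherit it or contradict it.

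**Conclusion.** The concern holds as a poor stated method of modest consequence. The rule offers essentially no precision over no adjustment (a change of −0.1 to −0.2 points in simulation A) and leaves the GEE/GENMOD and acceptability models open until the data are in.

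The forgone gain at 24 weeks postpartum is about 1–5 percentage points of power. It assumes two predictors at 0.3–0.8 log-odds per SD and was simulated for a single time point, not for the full repeated-measures GEE. At late pregnancy it is negligible. No size is claimed for the acceptability data, for which the Protocol gives no effect size or power. The case against the rule itself does not depend on predictor strength, since the imbalance condition alone blocks most useful adjustment. It should be changed, but it does not threaten the trial's validity.

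**What to change.** - Delete the baseline-test rule from both places in Statistical Methods, and keep the baseline table descriptive, without p-values.
- Name one or two intake smoking covariates for the GEE/GENMOD abstinence models before outcome data are seen, for example cigarettes per day and time to first cigarette. Use them whatever the observed balance.
- Keep the clinic-stratified C-M-H tests as stated. Report the unadjusted result next to the adjusted one, saying which odds ratio each is.
- Fix any covariates for the acceptability ANOVAs in advance in the same way.

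The cost is a few sentences of text. The variables are already collected, so there is no added burden on participants. The downside is that about 19 expected events at 24 weeks allow only a very short list, and the benefit will be small if the chosen variables predict abstinence weakly.

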#### Sample Size Justification

Based on data from (a) our prior and ongoing trials which utilized a comparable schedule of routine smoking monitoring visits and schedule of potential earnings, and (b) previous trial data indicating a 20% decrease in abstinence rates from late pregnancy to 24-weeks postpartum, we expect late-pregnancy abstinence rates of approximately 40% vs. < 10% (incentives vs. best practices, respectively), and 24-week postpartum abstinence rates of approximately 20% vs. < 5%. The proposed sample size of 76 per treatment condition will result in at least 80% power to detect a difference between the two treatment conditions in abstinence rates of 40% vs. 10 % at late-pregnancy or 20% vs. 5% at 24-weeks postpartum assessments using a chi-square test. This proposed sample size is also expected to be more than sufficient for examining differences between treatment conditions in birth weight and breastfeeding outcomes. With respect to mean birth weight, power is estimated to be 60% to detect a difference of approximately 200 g between the incentives versus best practices conditions assuming a pooled standard deviation (SD) of 550 g, which aligns well with treatment effects in our study aggregating birth outcomes across our first three controlled trials whereby mean birth weights were  $3295.6 \pm 588$  g vs.  $3093.6 \pm 404$  g in the incentives versus control conditions, respectively. We are estimating breastfeeding rates of 50% and 30% in the incentives condition and 17% and 13% in the best practices condition at 12 and 24-weeks postpartum based on our prior study results. Using chi-square tests, we will have over 75% power to detect differences in breastfeeding rates between the incentives versus best practices conditions at the two assessments. Power calculations were done using a two-sided significance level of 0.05. A sample size of 60 for the arm targeting AI/AN women was selected based on initial pilot studies of the financial-incentives-based approach to promoting smoking cessation among pregnant women developed at the University of Vermont (Higgins et al., 2004). This sample size will be sufficient to determine whether the intervention is feasible and effective at promoting late-pregnancy smoking abstinence between AI/AN women enrolled in the Incentives versus Best Practices Control conditions. Results of our assessment will be used to inform power analysis calculations for larger-scale, NIH-supported research proposals focused on smoking cessation among AI/AN pregnant women.

**Risks/Benefits:** Describe any potential or known risks. This includes physical, psychological, social, legal or other risks. Estimate the probability that given risk may occur, its severity and potential reversibility. If the study involves a placebo or washout period, the risks related to these must be addressed in both the protocol and consent. Describe the planned procedures for protecting against or minimizing potential risks and assess their likely effectiveness. Where appropriate, discuss plans for ensuring necessary medical or professional intervention in the event of adverse effects to the subjects. Discuss the potential benefits of the research to the subjects and others. Discuss why the risks to the subjects are reasonable in relation to the anticipated benefits to subjects and others. Discuss the importance of the knowledge gained or to be gained as a result of the proposed research and why the risks are reasonable in relation to the knowledge that reasonably may result. If there are no benefits state so.

#### Risks

Participants may experience some discomfort arising from nicotine withdrawal. Participants will be informed during the informed consent process that they may experience the following symptoms of nicotine withdrawal: craving cigarettes, restlessness, irritability, increased appetite, increased eating, dizziness, difficulty concentrating, and depressed mood. There is a small risk that participants' electronic information could be accessed thereby affecting confidentiality. There is a risk that women may be uncomfortable answering some of the questions on the formal assessment batteries. There is a risk that use of other combustible tobacco products and/or marijuana during study participation may elevate participants' breath CO levels thereby preventing them from earning incentives during week 1 even if they have quit smoking cigarettes. Similarly, use of other nicotine products like e-cigarettes or nicotine replacement therapy could elevate salivary cotinine levels after week 1 and prevent subjects from earning incentives. There is also a risk that a participant may become distraught during the course of the study and become a danger to herself, or that other emergencies could arise that research staff may need to address.

### Summary of Protection Against Potential Risks

We will take the following actions to protect against potential risks: (a) We will inform women during the informed consent process that reducing and/or quitting smoking may result in nicotine withdrawal symptoms however these symptoms should disappear within two weeks. (b) To ensure participant confidentiality, all study files will be stored in locked filing cabinets. All participants receive a subject identification code that is used in place of their name in all study files. The key connecting names and ID codes is kept in a locked file and stored separately from the data files. Study computers are password protected and encrypted. These protections apply only to study data collected via paper/pencil methods (e.g., phone eligibility screening data recorded by research staff). (c) For subjects who self-refer and complete their preliminary eligibility screening online, the survey will be administered using UVM's REDCap system. REDCap (Research Electronic Data Capture) is a secure, web-based application designed to support data capture for research studies that is hosted at UVM. REDCap has various security features, such as requiring usernames & passwords to access REDCap, and then needing permissions for the individual project. REDCap is accessed by URLs starting with HTTPS which encrypts data before being sent over the internet. (d) With respect to the assessment batteries conducted using REDCap or SurveyGizmo, we will not ask participants to self-report identifying information and both the REDCap and SurveyGizmo platforms are configured such that they do not retain identifying information (including IP addresses), thus a breach of confidentiality is exceedingly unlikely. (e) Participants will be informed during the informed consent process and again before completing the assessment batteries that they may skip questions or stop at any time should they feel uncomfortable answering some of the items. (f) Regarding the use of other tobacco products, we will inform women that the use of other combustible products could influence their breath CO and thereby limit their ability to earn incentives during week 1, and that using other nicotine-containing products following week 1 could influence saliva cotinine levels thereby preventing them from earning incentives from week 2 onwards. (g) If the investigative team or research staff are concerned that a given participant may be experiencing untreated psychiatric, family/social or other problems (e.g., suicidal thought), this information will be immediately acted upon by staff and investigators (e.g., crisis services in the participant's community will be contacted). Research staff will be trained to deal with emergency calls. Protocols for assessing and responding to suicidality include a suicidality assessment checklist and a plan to call Crisis Services if any intent is demonstrated.

The study investigators will oversee all procedures designed to continuously monitor participant safety. The investigative team will meet once each week to discuss actual or potential issues for each participant. During these meetings, investigators will review all participants' progress to ensure treatment fidelity

